**Figure 1 F1:**
[figure not shown]
Flow chart of study protocol. VAS, Visual Analogue Scale; SF-36, 36-Item Short Form Health Survey.

Predischarge, and 1 week, 1 and 3 months, 1 and 2 years after surgery: pain, wound infection, haematoma and seroma in the inguinal region and hernia recurrence will be recorded. Medical costs during hospitalisation and patient quality of life after discharge will be also recorded. The flow chart of study protocol is shown in figure 1. And The Standard Protocol Items: Recommendations for Interventional trials (SPIRIT checklist (Standard Protocol Items: Recommendations for Interventional Trials)) was followed in designing the study protocol (see online supplementary file 2).

10.1136/bmjopen-2017-016481.supp2Supplementary file 2

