### Follow-up

Visit 3 (1 week after surgery via clinic visit or telephone follow-up)36-Item Short Form Health Survey (SF-36) score;Medical costs;Hernia recurrence (date and severity of recurrence). Recurrence will be diagnosed by the medical institutions, after being alerted by patients that symptoms are present.Presence or absence of haematoma and/or seroma;Wound infection (date and severity of wound infection).

Visit 4 (1 month after surgery via clinic visit or telephone follow-up)SF-36 score;Medical costs;Hernia recurrence (date and severity of recurrence). Recurrence will be diagnosed by the medical institutions, after being alerted by patients that symptoms are present.Presence or absence of haematoma and/or seroma;Wound infection (date and severity of wound infection).

Visit 5 (3 months after surgery via clinic visit or telephone follow-up)SF-36 score;Medical costs;Hernia recurrence (date and severity of recurrence). Recurrence will be diagnosed by the medical institutions, after being alerted by patients that symptoms are present.Presence or absence of haematoma and/or seroma;Wound infection (date and severity of wound infection).

Visit 6 (1 year after surgery via telephone follow-up)VAS pain score;SF-36 score;Medical costs;Hernia recurrence (date and severity of recurrence). Recurrence will be diagnosed by the medical institutions, after being alerted by patients that symptoms are present;Presence or absence of haematoma and/or seroma;Wound infection (date and severity of wound infection).

Visit 7 (2 years after surgery via telephone follow-up)VAS pain score;SF-36 score;Medical costs;Hernia recurrence (date and severity of recurrence). Recurrence will be diagnosed by the medical institutions, after being alerted by patients that symptoms are present;Presence or absence of haematoma and/or seroma;Wound infection (date and severity of wound infection).

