### Outcome measures

#### Primary outcome measure

To reduce the outcome bias of a single evaluation, the incidence of chronic pain at 1 and 2 years after surgery will be evaluated. According to International Association for the Study of Pain, VAS pain score >0 for over 3 successive months indicates chronic inguinal pain.^20^

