### Patient completion/withdrawal from clinical study

Patients for whom the whole clinical data of at least 1 year are collected will be considered as complete cases. Patients with any one or more of the following criteria will be considered withdrawn from the study: mistakenly recruited, withdrawal of informed consent, on the request of the sponsor for safety reasons or patient conflicts or lost to follow-up. The date and reasons for withdrawal will be recorded on the eCRF. After termination of the study, the data collected at the last visit will be evaluated, except for data from those lost to follow-up.

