### Statistical analysis

Statistical analysis will be performed by a statician using SPSS V.19.0 software (SPSS). Continuous variables will be statistically described using the mean, SD, median, minimum and maximum. The categorical variables will be expressed using numbers and percentages.

The analysis will be performed on the basis of the intention-to-treat principle. Descriptive statistics of baseline information will be performed. The χ^2^ test or Fisher's exact test will be used for analysis of categorical variables, such as the incidence of postoperative chronic pain (primary outcome measure) and the incidence of postoperative complications (secondary outcome measure) between groups. Independent sample t-test or Mann-Whitney U test will be used for comparisons of continuous variables, such as SF-36 score, between groups. Cost-utility analysis will be used for economic evaluation, and sensitivity analysis of cost and utility will be performed.

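### Sponsor-requested withdrawal has no time limit and no provision for continued outcome follow-up, so a patient withdrawn before 1 year has no usable score for the primary outcome

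*Protocol article*

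**What the plan says.** In the protocol article, under Patient completion/withdrawal from clinical study, the grounds for counting a patient as withdrawn include "on the request of the sponsor for safety reasons or patient conflicts or lost to follow-up". The section does not confine the sponsor's request to any period and does not define a patient conflict. It requires the date and reason to be entered on the eCRF. On the data, it says: "After termination of the study, the data collected at the last visit will be evaluated, except for data from those lost to follow-up". It also says: "Patients for whom the whole clinical data of at least 1 year are collected will be considered as complete cases".

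The parts of the article that depend on this rule are:

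- **Primary outcome measure:** "the incidence of chronic pain at 1 and 2 years after surgery will be evaluated", with the definition that "VAS pain score >0 for over 3 successive months indicates chronic inguinal pain".
- **Follow-up:** the first postoperative VAS is at "Visit 6 (1 year after surgery via telephone follow-up)VAS pain score". The 1-week, 1-month and 3-month visits list SF-36, costs and complications, but no VAS. Table 3 likewise marks VAS only at visits 6 and 7.
- **Study design, text after Figure 1:** "Predischarge, and 1 week, 1 and 3 months, 1 and 2 years after surgery: pain, wound infection, haematoma and seroma" are recorded, with no pain scale named. The Abstract also places primary outcome assessments at every visit from baseline onward.
- **Statistical analysis:** "The analysis will be performed on the basis of the intention-to-treat principle".
- **Serious adverse event emergency reporting:** SAEs are followed until resolved or stable, even in patients who have stopped. Nothing comparable is stated for the pain outcome.

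**The concern.** Both arms receive one operation. After it there is no continuing study treatment to stop, so being withdrawn from the study can only mean that data are no longer collected. The grounds may be related to outcome. Table 3 lists wound infection, haematoma, seroma and recurrence as adverse events, and the section on AE and serious AE makes readmission and symptomatic recurrence SAEs, so a safety reason can overlap with a measured result. The term for patient conflicts is open enough to include a dispute over the result of surgery.

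An intention-to-treat comparison of chronic pain needs the 1- and 2-year outcome of every randomised patient. If patients who leave by this path are more likely to have pain, the observed rates fall. If the path is used differently by arm, the difference can move either way. This is a rule of conduct: an analysis plan can say how to handle a missing score but cannot restore one that was never collected.

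**Working it through.** **1. What a withdrawn patient contributes to the primary outcome**

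- *Withdrawn before 1 year.* By the visit list and Table 3, the only VAS on file is the preoperative one. The last-visit rule excludes only patients lost to follow-up, so it applies here, but it offers a score taken before the operation.
- *If pain is in fact recorded earlier.* The Abstract and the text after Figure 1 suggest this, and SF-36, collected from 1 week, has a bodily pain scale. These passages must be reconciled with the visit list. Even so, records up to 3 months could hardly show VAS above 0 for over 3 successive months at 1 or 2 years.
- *Withdrawn between 1 and 2 years.* The 1-year VAS exists and only the 2-year score is lost.

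**2. The plan's own figure**

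Inputs from Sample size: p1 = 0.10 (anterior), p2 = 0.034 (preperitoneal), α = 0.05, power 90%. Two-sided testing and 1:1 allocation are assumed, as neither is stated there. With mean rate 0.067 and pooled variance:

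n per arm = [1.960·√(2·0.067·0.933) + 1.282·√(0.10·0.90 + 0.034·0.966)]² / 0.066² = (0.693 + 0.449)² / 0.004356 ≈ 299.5, rounded up to 300.

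The total is 600, as stated. Expected events are 300 × 0.10 = 30 and 300 × 0.034 = 10.2.

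**3. Illustration of selective withdrawal**

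The article gives no rate for this path, so the shares are assumed. Remove a share w of the chronic-pain patients from an arm:

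observed rate = 300p(1 − w) / (300 − 300pw)

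power = Φ[(d − 1.96·SE₀)/SE₁], where d is the observed difference, SE₀ is the pooled and SE₁ the unpooled standard error.

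| Share removed | Anterior | Preperitoneal | Difference (points) | Power |
|---|---|---|---|---|
| none | 30/300 = 10.0% | 3.4% | 6.6 | 90% |
| 10%, both arms | 27/297 = 9.1% | 3.1% | 6.0 | 87% |
| 20%, both arms | 24/294 = 8.2% | 2.7% | 5.4 | 83% |
| 30%, both arms | 21/291 = 7.2% | 2.4% | 4.8 | 78% |
| 10%, anterior only (3 patients) | 9.1% | 3.4% | 5.7 | 82% |
| 20%, anterior only (6 patients) | 8.2% | 3.4% | 4.8 | 70% |
| 30%, anterior only (9 patients) | 7.2% | 3.4% | 3.8 | 55% |
| 20%, preperitoneal only (2 patients) | 10.0% | 2.7% | 7.3 | 95% |

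The last row shows that the difference can also be inflated. If both true rates were 10%, removing 10%, 20% or 30% of pain patients from one arm would raise the two-sided false-positive rate to about 6.6%, 12.1% or 22.5%.

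**4. If withdrawn patients stay in the denominator**

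Suppose they are kept and scored as pain-free. With anterior-arm withdrawal only, the differences are 27/300 − 3.4% = 5.6, 24/300 − 3.4% = 4.6 and 21/300 − 3.4% = 3.6 points. With both arms they are 9.0 − 3.06 = 5.9, 8.0 − 2.72 = 5.3 and 7.0 − 2.38 = 4.6 points. Keeping them without a real outcome does not remove the problem. If a preoperative VAS above 0 were instead counted as pain, the result would reflect pain before surgery.

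**The case against.** The wording is generic. It does not mention operated patients, pain or dissatisfaction, and consent and the eligibility recheck come before surgery, so the ground may be meant for that period. The reason for each withdrawal is recorded and can be audited, and SAEs are followed regardless. The handling of missing outcomes is commonly left to the analysis plan. No document supports the sponsor removing 10–30% of pain patients, still less in one arm. With equal shares in both arms the risk ratio barely moves (10/3.4 = 2.94; 7.2/2.4 = 3.0).

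Much of this stands. A reader might infer that the sponsor will remove operated patients because they did badly, and that the primary comparison is therefore biased. The article supports neither: it permits such use but does not describe it, and the bias is possible rather than shown. A reader might also infer that no pain information at all exists before 1 year. That goes too far, given SF-36 bodily pain and the earlier pain assessments mentioned in the Abstract and after Figure 1. Only a scheduled postoperative VAS is absent. Nor does the article's silence on whether the sponsor is blinded prove anything, since it is a condensed text.

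What the objection does not answer is that the rule has no time limit and leaves outcome follow-up open. An audit trail and SAE reports do not supply a 1- or 2-year VAS.

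**Conclusion.** The point holds as a defect in the withdrawal rule that should be corrected because it is cheap to close. As written, the rule lets a randomised patient leave outcome follow-up at the sponsor's request, on grounds that may be related to outcome. Before 1 year, neither the last-visit rule nor the intention-to-treat statement then yields a valid primary outcome.

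The possible effect is material because so few events carry the trial: power falls to 87–78% if 10–30% of chronic-pain patients are lost in both arms, and to 82–55% if only in the anterior arm. These figures rest on the planned 10% and 3.4%, on 300 evaluable patients per arm, on two-sided testing and on assumed withdrawal shares. They show sensitivity and do not forecast what will happen. Withdrawal unrelated to pain would cost precision without this bias.

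**What to change.** Amend Patient completion/withdrawal from clinical study to say that:

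- a sponsor decision does not end outcome collection, and the 1- and 2-year VAS is sought in every randomised patient unless the patient withdraws consent to data collection;
- the safety problem or dispute is recorded as an event, with its reason;
- these patients stay in the primary intention-to-treat analysis;
- the preoperative VAS is not used as their outcome.

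This leaves the sponsor's safety-based right untouched and separates it from data collection. In the same amendment, reconcile the Abstract and the text after Figure 1 with the visit list and Table 3 on when pain is assessed and on what scale.

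The cost is a short change of text and a few extra telephone contacts, as the Follow-up section already makes both visits by telephone. The downside is that some of these contacts will be with dissatisfied patients.

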### Statistical analysis

Statistical analysis will be performed by a statician using SPSS V.19.0 software (SPSS). Continuous variables will be statistically described using the mean, SD, median, minimum and maximum. The categorical variables will be expressed using numbers and percentages.

The analysis will be performed on the basis of the intention-to-treat principle. Descriptive statistics of baseline information will be performed. The χ^2^ test or Fisher's exact test will be used for analysis of categorical variables, such as the incidence of postoperative chronic pain (primary outcome measure) and the incidence of postoperative complications (secondary outcome measure) between groups. Independent sample t-test or Mann-Whitney U test will be used for comparisons of continuous variables, such as SF-36 score, between groups. Cost-utility analysis will be used for economic evaluation, and sensitivity analysis of cost and utility will be performed.

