**Methods and analysis:**

This will be a prospective, large sample, multicentre, randomised, controlled trial. Registration date is 1 December 2016. Actual study start date is 6 February 2017. Estimated study completion date is June 2020. A cohort of over 720 patients with inguinal hernias will be recruited from nine institutions in Liaoning Province, China. Patient randomisation will be stratified by centre to undergo inguinal hernia repair via the anterior transversalis fascia approach or the preperitoneal approach. Primary and secondary outcome assessments will be performed at baseline (prior to surgery), predischarge and at postoperative 1 week, 1 month, 3 months, 1 year and 2 years. The primary outcome is the incidence of postoperative chronic inguinal pain. The secondary outcome is postoperative complications (including rates of wound infection, haematoma, seroma and hernia recurrence).

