**Trial registration number:**

NCT02984917; preresults.

Strengths and limitations of this studyThis trial will be the first prospective multicentre randomised controlled study involving nine institutions in Liaoning province of Northern China to provide reliable results from a representative study population.This trial will compare postoperative complications after anterior transversalis fascia approach versus preperitoneal space approach for inguinal hernia repair in residents in Northern China.Based on ethical and economic considerations, interim analysis will be performed during the trial to reduce unnecessary waste of manpower and materials (lower cost).The limited time for studying postoperative recurrence of hernia likely influences the judgement of long-term recurrence of inguinal hernia.Variability of surgeons from each study centre could be a major confounder to bias the results of this trial.

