### Distinguishing features from related studies

(1)This study will use centre-based stratification to investigate the effects of anterior transversalis fascia approach versus preperitoneal space approach for inguinal hernia repair on postoperative chronic inguigal pain and other common complications. This study will determine the optimal surgical hernia repair approach that is suitable for the anatomic characteristics of the inguinal region of residents in northern China and corresponds to the regional economic conditions. (2) Cost-utility analysis will be analysed using centre-based stratification. (3) To analyse the effects of different surgical repair approaches (involving various patch types and materials) on postoperative quality of life.

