### Randomisation and blinding

This study is a multicentre trial, so stratified block randomisation will be performed in each centre. A randomisation sequence table will be generated by a statician who will not be involved in the trial using Statistical Analysis System (SAS V.9.1). The serial numbers assigned to each patient will be preserved in opaque sealed envelopes. The sealed envelopes will be subsequently given to the trial centre. All patients will not know the surgical regimen until after the surgery. The surgeons will not be blinded to the surgical regimen. Outcome assessors will be blinded to the surgical records in the electronic case report form (eCRF).

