### Study flowchart

#### Before surgery

Visit 1 (at admission, day 0)Sign informed consent;Recheck inclusion/exclusion criteria;Demographic data (sex, age, body height, body mass index) and medical insurance type;Type of hernia (indirect or direct);Inguinal hernia classification as type I, II, III or IV according to the adult inguinal hernia and femoral hernia classification (revised in 2003) developed by the Hernia and Abdominal Wall Surgery Group, Society of Surgery, Chinese Medical Association^19^;ASA classification;History of diseases and risk factors* (diabetes mellitus, cardiovascular disease, lung disease, peripheral vascular disease, dementia, hypertension, smoking history and alcohol use history) (*optional evaluation items);Disease onset and admission (interval from first appearance of the lump, main symptoms);Imaging examination (ultrasound, CT);Laboratory examination (routine blood testing, coagulation testing, testing of blood glucose, lipids and electrolytes and hepatic and renal function);Vital signs (body temperature, pulse, respiration rate, blood pressure);VAS pain score;Electrocardiography;Concomitant treatment.

The baseline information of patients with inguinal hernia included in this study is shown in table 2.

**Table 2 T2:** Baseline information of patients with inguinal hernia

Sex	Smoking history
Age	History of alcohol use
Body height	Disease attack and admission
Body mass index	Laboratory examination
Medical insurance type	Imaging examination
Type of hernia	Vital sign
Inguinal hernia classification	VAS pain score
Treatment time	ECG
American Society of Anesthesiologist Classification	Concomitant therapy
History of diseases	
Diabetes mellitus	
Cardiovascular disease	
Lung disease	
Peripheral vascular disease	
Dementia	
Hypertension	

VAS, Visual Analogue Scale.

Predischarge

Visit 2Vital signs (body temperature, pulse, respiration rate, blood pressure);Laboratory examination (routine blood testing, coagulation testing, testing of blood glucose, lipids and electrolytes and hepatic and renal function);Treatment regimen (inguinal hernia-specific treatment).

Surgical approach and patches (type and fixation method); anaesthesia method; drug name (generic preferred), dosage, route, start date, length of drug use will be recorded.Medical costs;Concomitant treatment.

Inguinal hernia-specific treatment, maintenance therapy and drugs used for concomitant treatment.Medical costs because of adverse events (AE).

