## Discussion

### Significance of this study

This study will be the first large sample (720 patients), multicentre, randomised, controlled, clinical trial to investigate the effectiveness of inguinal hernia repair via the anterior transversalis fascia approach versus the preperitoneal approach in patients from northern China. In this study, postoperative complications will be used as the primary outcome measure, and patient quality of life and cost-utility analysis will be the secondary outcome measures.

However, this study is also limited: (1) Although all surgeons involved in the study will receive training of standard surgical procedure, confounding variables including surgeon’s clinical experiences and surgical conditions should be considered to reduce the bias in the estimate of the study outcomes. (2) The time taken for studying postoperative recurrence of inguinal hernia is limited, which likely influences the judgement of long-term recurrence of inguinal hernia.

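### Randomisation is blocked within nine centres, but the binary outcomes are tested without centre: a valid, slightly conservative choice that can be aligned with the design at almost no cost

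*Protocol article*

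**What the plan says.** **Design.** The abstract states that "Patient randomisation will be stratified by centre to undergo inguinal hernia repair", with patients "recruited from nine institutions in Liaoning Province, China". The section Randomisation and blinding adds that "stratified block randomisation will be performed in each centre".

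**Analysis.** The section Statistical analysis names a χ² or Fisher test for the primary outcome and for postoperative complications: "exact test will be used for analysis of categorical variables, such as the incidence of postoperative chronic pain (primary outcome measure". The comparison is between groups, with no stratum, centre term or covariate.

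**Announced approach.** Under Distinguishing features from related studies, item 1 reads "This study will use centre-based stratification to investigate the effects of anterior transversalis fascia approach versus preperitoneal space approach". Item 2 applies the same phrase to the cost-utility analysis.

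**Related statements.** The strengths and limitations list warns: "Variability of surgeons from each study centre could be a major confounder to bias the results of this trial". The Discussion says that surgeon experience and surgical conditions "should be considered to reduce the bias in the estimate of the study outcomes". A pain score is among the preoperative items ("VAS pain score;Electrocardiography;Concomitant treatment"), but Table 3 marks the VAS only at the last two visits.

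**The concern.** Blocks within centre remove between-centre differences from the comparison of arms. An unstratified test still counts those differences as noise, so its standard error is somewhat too large whenever centres differ in pain rate. The analysis then gives back a little of what the stratified design gained.

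There is also a question of consistency. A reader of the distinguishing-features section may expect a centre-stratified comparison, while the analysis section describes an unstratified one. With only about 40 events expected, a borderline result is possible. It should be settled before outcome data are seen which of the two analyses is primary.

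**Working it through.** **1. The plan's own figure.** Inputs from Sample size: 10% and 3.4%, α = 0.05, power 90%. Two-sided testing and 1:1 allocation are assumed, since neither is stated. With a mean rate of 0.067:

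n per arm = [1.960·√(2·0.067·0.933) + 1.282·√(0.10·0.90 + 0.034·0.966)]² / 0.066² = (0.693 + 0.449)² / 0.004356 = 299.5, so 300 per arm and 600 in all.

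This matches the stated 600. The trial is sized for the unadjusted two-proportion test, so the stated test and the stated sample size agree.

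**2. Why centre matters.** With equal allocation in every centre, the unstratified test uses the variance p̄(1−p̄). The variance that applies is the average of p_k(1−p_k) over centres, which is p̄(1−p̄) minus the between-centre variance of the p_k. The unstratified test is therefore conservative when centres differ, and the two agree when they do not.

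**3. Size, by simulation.** The documents give no between-centre variance, so a range is assumed. Set-up: nine equal centres with 33 patients per arm each (9 × 2 × 33 = 594); normal centre effects on the logit scale; marginal rates held at 10% and 3.4%, or 6.7% in both arms under the null; 20,000 trials per row; χ² without continuity correction.

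| Centre SD (logit) | Type I error, χ² | Type I error, CMH | Power, χ² | Power, CMH |
|---|---|---|---|---|
| 0 | 5.1% | 5.0% | 91.5% | 91.4% |
| 0.3 | 5.1% | 5.1% | 91.4% | 91.3% |
| 0.5 | 4.6% | 4.6% | 90.5% | 90.6% |
| 0.8 | 4.8% | 5.1% | 90.5% | 90.8% |
| 1.2 | 4.3% | 5.1% | 89.5% | 90.2% |

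Monte Carlo standard errors are about √(0.05·0.95/20,000) = 0.15 points for type I error and √(0.9·0.1/20,000) = 0.21 points for power. Simulated power at SD 0 lies about 1.5 points above the formula's 90.0%, so compare within rows. Across the rows, CMH differs from χ² by −0.1 to +0.7 points of power.

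A second run used 720 × 0.8 = 576 patients and a 10% null rate. At SD 1.0, type I error was 4.3% (χ²) against 5.1% (CMH), and power 88.7% against 89.4%. At SD 1.5 the figures were 3.5% against 4.9%, and 88.1% against 89.3%. At a 10% marginal rate, SD 1.0 puts 95% of centres between about 1% and 35%, and SD 1.5 between about 0.3% and 50%. Those are very wide spreads.

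**4. Events per stratum.** 300 × 0.10 + 300 × 0.034 = 30 + 10.2, about 40 events, or 40/9 ≈ 4.4 per centre. CMH copes with this. A logistic model with eight centre indicators and further covariates is sparse.

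**5. Baseline pain score.** Four scenarios were assumed: (centre SD, log odds ratio per SD of score) = (0, 0.3), (0.5, 0.5), (0.8, 0.5), (0.5, 0.8). A logistic model with centre and score gave power 92.5, 92.0, 90.6 and 92.2%, against 92.0, 91.4, 89.5 and 91.0% unadjusted. The gain is about 0.5 to 1.2 points. These runs had 2,000 trials each (standard error about 0.7 points), and the model's type I error was 0.2 to 0.8 points above that of χ². The gain is small and not all of it is precision.

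**The case against.** The strongest reply is that almost nothing is at stake. At a between-centre SD of 0.5 the two tests cannot be told apart. A visible gap needs centre rates spread far more widely than seems likely for male, ASA I–II patients with primary unilateral hernia in one province. That stands: the gain is at most about 1 point unless centres differ very widely.

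Three stronger readings are tempting, and the documents do not support them.

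- **That the primary test is invalid or its precision badly misstated.** It is valid and errs, slightly, on the safe side. The sample size also agrees with it.
- **That ignoring centre leaves the comparison confounded.** Blocks within centre balance the arms by centre, so centre affects precision, not bias. Surgeon confounding would arise within centres if different surgeons performed the two approaches. The article does not say whether they do, and it does say that all surgeons receive training in the standard procedure. A centre-stratified test would not remove such confounding. A surgeon term might not either, because surgeon and arm would then largely coincide.
- **That the article contradicts itself.** Item 1 of the distinguishing features can describe stratified randomisation just as well. Item 2, on cost-utility, leans towards analysis. This is an ambiguity to reconcile, not a proven contradiction.

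It may also be said that such detail belongs in a statistical analysis plan that is not shown. That holds for supportive models and surgeon effects, which are not counted here as missing. It does not hold for the primary test, which the article names.

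**Conclusion.** The point holds as a modest one of consistency and precision. Randomisation is stratified by centre, and the named tests for the primary and secondary binary outcomes are not. Under assumed between-centre SDs of 0 to 1.2 on the logit scale, the unstratified test's type I error goes from about 5% to 4.3%, and its loss of power is 0 to 1 point. If centres are alike, stratifying costs about 0.1 point, which is within simulation error.

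The figures rest on equal centre sizes, 1:1 allocation, normal centre effects and the planned 10% and 3.4%. They were run for the χ² test, not for Fisher's. No conclusion about bias follows, and the surgeon variability that the article raises is a separate matter that this change does not settle.

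**What to change.** In Statistical analysis:

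1. Make the primary test a Cochran-Mantel-Haenszel test stratified by centre, and report the Mantel-Haenszel risk difference with its 95% CI.
2. Use the same method for secondary complication rates where events allow. Keep an exact test for the rarest ones.
3. Keep the unadjusted χ² or Fisher test as a sensitivity analysis.
4. State under Distinguishing features whether centre-based stratification means randomisation, analysis or both, and make the two sections agree.

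Adjustment for the preoperative VAS is optional and supportive only. Before it is used, Table 3 must be reconciled with Study design and the visit 1 list, which both include a preoperative score.

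The cost is a few sentences. Centre is known for every patient because it is the randomisation stratum, the procedures are standard, and the sample size does not change. The change should be dated before the first interim analysis, so that the choice is made without sight of outcomes.
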